## **DATA AND SAFETY MONITORING PLAN**

The primary human subjects in this proposal are the adult physicians, nurses and office staff members whose behavior we will change to provide best-practice care for diagnosing and providing initial management for pediatric hypertension (HTN). We will collect pediatric patient HTN error data as a marker of this behavioral change but there will be no children directly involved in the research as study subjects. The project aims to aid clinicians in implementing best-practice, guideline recommended care around pediatric HTN. For this reason, this proposal is minimal to no-risk. Additionally, as practices will necessarily be aware of the quality improvement collaborative group they were randomized to, no data will be blinded. The proposal uses a stepped-wedge design, allowing all randomization cohorts to eventually receive the full intervention in order to meet clinical equipoise. All data will be fully transparent between quality improvement collaboratives to ensure maximal improvement on these standard-of-care measures. We have scheduled interim data analysis steps every six months of the project (6, 12 and 18 months) after the beginning of intervention, and our collaboratives will review data on a monthly basis in real time to ensure no unintended consequences of the project. [name], Senior Biostatistician at the Albert Einstein College of Medicine, will ensure correct and statistically valid data analyses. Due to the minimal to no-risk nature of the study, the unblinded data collection, the standard of care of these interventions, and the real-time interim data analyses as part of the quality improvement collaborative, a formal Data and Safety Monitoring Board is not necessary. Oversight and monitoring to ensure the safety of participants and the validity and integrity of the data will be ensured by the entire research team, with particular focus by the PI and core leadership team: Drs. [name], [name] and [name].

Although unlikely given the standard nature of primary and secondary outcome measures in this project, if any practice sites are unable to collect data for any reason, they will be coached and attempts will be made to facilitate data collection. If they are still unable to collect data, the stopping rules at which time the practice will be asked to leave the project will include inability to collect data for 2 months following data coaching interaction. It is incredibly unlikely that any Adverse Events or Serious Adverse Events will occur as part of this standard of care study. If any do occur, or an Unanticipated Problem occurs, the PI, [name], will take full responsibility, immediately report the event to the research team, the lead-site's IRB (Einstein/Montefiore), the local site's IRB, the Agency for Healthcare Research and Quality, and other appropriate offices or agencies as needed.

Finally, all data from all sites will be entered into a REDCap data base. Data capture will be centralized via direct patient data entry or electronic data transfers into this REDCap database. REDCap is web-based and HIPAA compliant, and [name] and Einstein/Montefiore will take responsibility for data security. These data will not include patient names, dates of birth, or medical record numbers. As noted above, we will employ an "honest broker" for our REDCap database with regards to clinic visit dates. [name] has functioned in this role before and will create 2 separate REDCap databases. Participating clinics will have access to and enter data in a REDCap database that includes visit dates. The research team will never have access to this database. The second REDCap database, accessible by the research team, will receive days elapsed between clinic

visit dates data from the first database, but no specific clinic visits dates. [name] will ensure the research team never receives any PHI from clinics.

The grant supports an experienced REDCap data analyst at Montefiore/Einstein to create and manage these platforms and assist sites in data collection. REDCap is web-based and HIPAA compliant, and [name] and Einstein/Montefiore will take responsibility for data security. REDCap will disseminate monthly feedback reports with full transparency and benchmarking to intervention practices. Practices and hypertension specialists will report demographic data annually, including patient volume, number and training level of providers, nursing and office staff, presence of trainees, and prior work aiming to improve HTN errors and QI context. Data collection sheets (see appendix) will assist practice teams in chart review and will mimic the REDCap database appearance.

Practice groups will work with the research team to create systems for standardized data collection and data entry. An orientation session will teach practices to identify each phase of pediatric HTN and EBP diagnosis and management, reliably collect these data via chart review and/or EHR data pulls and enter data into a centralized database. The research team will assist with issues and distribute clarifications to all teams to aid in standardization. As all 6 initially recruited practice groups employ integrated EHRs, practices will likely collect the above data by employing EHR based record review or data pulls, depending on abilities and interest of local EHRs. These tools will ensure standardized data collection by disparate practices and were pilot tested at MMG and the Johns Hopkins Harriet Lane Clinic. The Montefiore/Einstein-based project manager, closely supervised by [name], will ensure accurate and timely data submission by each practice site. Data will be checked for outliers or abnormal values and feedback given to practices to ensure consistency across practices. Site leads will perform secondary chart reviews to confirm data accuracy and aid in standardization. [name] and this team successfully completed similar processes with 30 primary care pediatric practices for 24 months and 3 different pediatric errors without any funds to support obtaining data.

As noted above, each practice site will retrospectively identify the first 10 patients monthly with an elevated BP. Numbers of charts for review are based on power calculations and pragmatic considerations for busy PCPs. By selecting the first 10 patients with an elevated BP seen monthly, we ensure quasi-random selection of cases to review, while making data collection feasible. During the baseline period, this number will be 17 patients per month for 3 months, in order to provide an adequate baseline sample for practices to begin changing their practice. This pragmatic data collection will allow for greater generalizability of results and methods, and spread at the conclusion of the project. Each practice site will evaluate those patients following the elevated BP to confirm correct HTN and EBP diagnosis and management steps. Each step of the HTN diagnostic and management process will be checked and time stamped via standardized data collection sheets and/or EHR summary reports. As noted above, the research team will never have access to clinic visit dates, and these will be protected by [name], who will serve as the honest broker for this project. All segments of the EHR will be searched to confirm diagnostic and management steps. If not already present by the eighth patient's chart reviewed each month, practices will specifically search for and collect data from at least two patients who proceeded through the diagnostic work-up phase until initiation of HTN management, to ensure data capture on the complete HTN diagnosis and management process. As 3-5% of patients have HTN, this number of patients is obtainable in the primary care setting. Additionally, to ensure proper screening, all staff who routinely obtain patient BPs will complete a self- and/or observed audit form weekly on the 5 most important aspects of BP measurement during the QIC without subspecialist involvement until the site is consistently greater than 90% compliant. Finally, specialists will report time to 3rd next available appointment on the first of every month during the project's baseline and intervention periods.

For the 100 patients already identified by the study site as having an elevated BP measurement but no follow-up, data identified above will be collected. We will also collect data on manual in-clinic BP measurements, HBPM data, time between phone contact, receiving HBPM and returning data and ABPM data and nephrology follow-up data. All these data will be de-identified as described above and verbal phone consent will be obtained from caregivers and adult patients, and verbal assent will be obtained by the parent for children 7-17 years old. It is impractical for the study's one research assistant to be present at all 200 anticipated patient visits across 6 clinical sites to obtain in-person consent. Additionally, in the face of the COVID pandemic and the need to maintain social distancing, all MMG sites have restricted access to non-clinical research staff, especially in cases where consent and research processes can be conducted over the phone. Performing verbal consent will be safer for participants, the research assistant, and MMG staff in the involved sites. Additionally, it is challenging to obtain verbal assent from 7-17 year olds while on the phone, so we will ask the caregivers to perform that task under the research assistant's guidance. Paper versions of the completed consent form will be mailed to all participants. Providers and patients will be free to refuse to collect these data, refuse to receive the HBPM or the ABPM, or refuse to return to clinic as per normal care. See attached data collection form.

## **6. Statistical Analysis**

### **6.1 Statistical Models:**

The primary independent variable will be interventions with titrated QIC dosage levels stepped-up from the control condition (usual care) with scale scores from 0 (usual care) to 3 (hub and spoke). The primary dependent variable will be the proportion of all incorrect diagnostic and management decisions completed per 100 patients with elevated BPs. The individual-level outcome will be binary (incorrect or correct care), and absolute risk difference will be the primary measure of intervention effects. As there will be a multilevel hierarchy in the data structure, we will apply generalized mixed-effects models with identity link for testing the primary hypothesis in terms of risk difference. Site-specific, practice group-specific, and month-specific intercepts will be considered random to take into account potential variations in outcomes at all such levels in addition to correlations of individual-level outcome nested within each month for each practice. We will test if each step-up of the interventions (QIC without subspecialist, QIC with subspecialist, and hub and spoke) as compared to the control condition significantly reduce incorrect diagnosis and management proportions. We will also make all pairwise comparisons among the four conditions including usual care. All analyses will be controlled for potential confounding effects including factors such as baseline error rates, patient volume, number and training of providers, nursing and office staff, and prior work improving these errors.

For the secondary analyses testing 1) time to care, 2) sustainability, 3) change in collaborative effect for second wave and 4) necessity of PCP and subspecialist integration before hub and spoke model introduction, we will use all relevant QIC data. Each of these hypotheses will be tested with appropriate contrasts between intervention effect and the relevant group and time in generalized mixed-effects regression models. Testing the sustainability will be based on a contrast within Cohort 1.

The main outcome will be presented with descriptive statistics, examining the percent of patients who accepted the HBPM and returned data in a timely manner. We will also analyze the concordance between in-clinic manual BP measurements and the HBPM measurement averages.

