**Figure 2: 28 month collaborative structure, Winter 2018-Spring 2020**

The 6 committed practice groups have over 1,000 providers and 1.5 million pediatric patient visits annually. Each practice group, including additional ones not yet recruited, will receive approximately \$5,000 annually to fund data collection processes. Each of the at least 60 practice sites will identify a multidisciplinary team consisting of at least one physician, nurse and practice associate, allowing for improvement across disciplines. Teams will be supported by a pre-identified relevant and local HTN subspecialist.

Similar to our current diagnostic error QIC, we will apply multivariate matching to practice groups before randomization, which has been shown to provide more accurate effect estimates, creating an equivalent of 7% increase in sample size. Practice groups will be matched based on key demographics including 1) patient volume per practitioner +/- 100 patients, 2) patient population (rural, suburban or urban), 3) number of clinic sites, and 4) prior work reducing HTN diagnosis and management errors. These data as well as baseline demographic data and prior quality improvement experience data will be collected annually via the BP-CATCH Practice Inventory (attached). It will be completed by the lead practice physician following submission of a signed consent form to participate in the BP-CATCH project. The survey tool will be collected via SurveyMonkey, and administered at the start of the project, and twice annually thereafter. Similarly, we will administer a demographic survey to the hypertension subspecialists for each practice group. It will be completed by the hypertension subspecialist physician following submission of a signed consent form to participate in the BP-CATCH project. The survey tool will be collected via SurveyMonkey, and administered at the start of the project, and twice annually thereafter. Data from this survey will not be used in randomization. After matching, randomization will occur via computerized random number generation and practice groups will be assigned to one of 2 study cohorts.

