Both cohorts will collect 3 months of retrospective baseline data collection before beginning the study. During the first six months of the intervention, the practice groups randomized to Cohort 1 will begin working on improving HTN practices within their clinic via a QIC, while the other cohort will act as a control (usual care) with data collection (**Specific Aim 1**). Cohort 1 will attend an initial 1-day interactive video webinar learning session where they will learn QI methodology, enhance and practice QI skills, identify local 30-60 day aims to improve local HTN practices and increase their understanding of pediatric HTN. They will also begin tracking data on a HTN registry and learn how to ensure accurate BP measurement is completed in their clinic. They will participate in QI coaching, monthly video conferences, and monthly mini-root cause analyses (Mini-RCA) (see below). Cohort

2 will submit control data and not receive centralized data feedback. They will also begin tracking data on a HTN registry and learn how to ensure accurate BP measurement is completed in their clinic.

During the second 6 months, Cohort 1 will integrate their HTN subspecialist into the QIC and focus on issues at the boundary of PCP and subspecialty care (e.g. pre-referral work-up, communication across providers, and time for next available appointment). Cohort 2 will begin improving HTN practices within their clinics via a separate but comparable PCP-only QIC, (**Specific Aim 2**). In the third 6 months, Cohort 1 will continue QIC components and implement a hub and spoke model, where the PCP diagnoses and provides definitive management for pediatric HTN with subspecialist support and Cohort 2 will engage their HTN specialist (**Specific Aim 3**). In the final six months, Cohort 1 will sustain their changes, illustrating the durability of these system changes even after QIC completion. Cohort 2 will continue their QIC with the hub and spoke model.

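### Section 6.1 treats calendar month only as a random intercept, so a secular fall in errors would largely be read as an intervention effect, and the power claim in 6.3 depends on this choice

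*Protocol*

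**What the plan says.** Section 6.1 makes the primary exposure a dose score "with scale scores from 0 (usual care) to 3 (hub and spoke"), fitted in an identity-link mixed model. On the random part it says: "Site-specific, practice group-specific, and month-specific intercepts will be considered random", "in addition to correlations of individual-level outcome nested within each month for each practice". The adjustment sentence reads "All analyses will be controlled for potential confounding effects including factors such as baseline error rates" and goes on to patient volume, staffing and prior work. Calendar time is not on that list. Time appears only for the secondary hypotheses, which are to be "tested with appropriate contrasts between intervention effect and the relevant group and time in generalized mixed-effects regression models".

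Section 6.3 uses the same structure for power. Month is random variation of +/-15 points without a trend, the fitted model has random effects at all levels, and the stated result is more than 80% power for a 3-point fall per dose step.

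The schedule is in section 3 and Figure 2, where "practice groups will be assigned to one of 2 study cohorts". Cohort 1 starts the first collaborative in months 0-6, "while the other cohort will act as a control (usual care) with data collection". Each cohort then steps up every six months. "In the final six months, Cohort 1 will sustain their changes", while Cohort 2 reaches hub and spoke. Section 3 also records that the study stopped in March 2020 and that data from November 2018 to March 2020 will be analysed and published.

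**The concern.** In a stepped wedge the randomised evidence is the difference between cohorts in the same calendar period. Before-after change within a site is not randomised. A random month intercept assumes that month effects are unrelated to dose. Here they cannot be told apart well, because dose rises with the calendar in both cohorts. The dose term then explains a steady trend and the month variance is estimated as small.

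The protocol makes such a trend plausible. It describes the 2017 guideline as new. Both cohorts begin a registry and blood-pressure measurement training in Phase 1. Section 4 concedes that measuring errors in the control period may itself have an effect. At stake is the primary test, which could favour the collaborative when only time has passed.

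**Working it through.** **Inputs.** From 6.3: 7 practice groups, 60 sites, 24 months, 10 charts per site-month, ICC 0.5, baseline error rate 73%, +/-15 points at each level, two-sided alpha 0.05. From Figure 2: Cohort 1 doses 1, 2, 3, 3 and Cohort 2 doses 0, 1, 2, 3 over four six-month phases. Assumptions: the sustain phase is coded as dose 3, cohorts have 30 sites each, the trend is linear, and the true effect is zero.

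**Where the dose variation lies.** Mean dose by phase is 0.5, 1.5, 2.5, 3 (overall 1.875).
- Between months: 60 x 6 x (1.375² + 0.375² + 0.625² + 1.125²) = 360 x 3.6875 = 1327.5.
- Within months, after site effects: 360 x (3 x 0.125² + 0.375²) = 360 x 0.1875 = 67.5.
- Share between months: 1327.5 / 1395 = 95%. The correlation of mean dose with month is 0.96.

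**The plan's power figure.** The variance of a site-month proportion is v = 0.73 x 0.27 x (1 + 9 x 0.5) / 10 = 0.1084. With no calendar adjustment, SE = sqrt(0.1084 / 1395) = 0.88 points, and power at 3 points is Φ(3/0.88 - 1.96) = 93%. Simulation with site-specific month variation gives 90-92%. The stated figure is therefore reproduced. If the +/-15-point month variation is shared by all sites and fitted as a crossed random intercept, simulated power is only 39%.

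**Size of the bias.** The sum over months of (dose deviation x month deviation) is 1.375 x 54 + 0.375 x 18 + 0.625 x 18 + 1.125 x 54 = 153. Without calendar adjustment the bias per step is 60 x 153 / 1395 = 6.58 times the monthly fall: 1.6 points at 0.25 per month and 3.3 points at 0.5 per month.

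**Simulation, crossed random month fitted by REML, zero true effect:**

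| Schedule | Shared month noise | Fall per month | Estimate per step | False positives |
|---|---|---|---|---|
| 24 months | none | 0.25 | about -1.6 | about 35% |
| 24 months | none | 0.5 | about -3.3 | about 93% |
| 24 months | +/-15 points | 0.25 | about -1.4 | about 13% |
| 24 months | +/-15 points | 0.5 | about -2.5 | about 32% |

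The 35% varies with implementation, up to 48%. The SE per step is about 1.0 point in the first two rows and about 1.8 in the last two. If month is read as nested within site, the trend is not absorbed at all: a 10-point fall over 24 months gives -2.8 points per step and 93% rejection with no added month noise.

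**First-year data.** I assume 3 baseline months plus two six-month phases, with 10 charts per month throughout.
- Between-month sum of squares: 60 x (3 x 0.8² + 6 x 0.3² + 6 x 0.7²) = 324.
- Within-month: 60 x (3 x 0.4² + 12 x 0.1²) = 36. The between-month share is 324 / 360 = 90%.
- False positives are about 10% to 36% over the same trends and both noise settings.

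**Fixed month effects.** Bias is about 0 and rejection is 3-10% depending on implementation; Wald tests with 7 groups are slightly liberal. On 24 months, SE = sqrt(0.1084 / 67.5) = 4.0 points (about 3.7-4.2 across calculations). Power at 3 points is Φ(3/4.0 - 1.96) = 11%, or about 15% in simulation. The 80%-power step is 2.80 x 4.0 = 11.2 points, or 9.7 if the 3 baseline months are included. On the assumed first-year schedule, SE = sqrt(0.1084 / 36) = 5.5 points.

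**The case against.** The strongest defence has four parts.

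1. A random month intercept gives some protection. This is true but limited. For a 10-point fall over 24 months it removes only about 1% to 22% of the bias. With the plan's own month noise, the false-positive rate drops mainly because the standard error roughly doubles.
2. The adjustment list is open-ended, and a separate analysis plan could add time. However, 6.1 gives month an explicit role as random, and 6.3 is computed on that basis. This is a stated choice, not a detail left open.
3. The protocol gives no secular trend. This stands. Every bias and false-positive figure here is conditional on an assumed trend.
4. The 24-month design was abandoned. This also stands, and the first-year range is the more relevant one for what will be published. The structure is unchanged there, with 90% of dose variation between months.

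A reader might go further in three ways that the document does not support. First, 93% is not the plan's false-positive rate. It needs a 0.5-point monthly fall and no shared month noise, whereas 6.3 assumes +/-15 points for months. Second, a reader might infer that clustering by the randomised practice groups is ignored. Section 6.1 does include practice-group intercepts, and the document gives no variance from which to size any further group-by-time term. Third, monthly data feedback is not a source of secular trend. Section 3 makes it part of the intervention and withholds centralised feedback from the control cohort.

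**Conclusion.** The point holds. As written, the primary model draws almost all its information from non-randomised before-after change, and a secular fall in errors would largely be credited to the intervention. An assumed fall of 0.25 to 0.5 points per month yields about -1.4 to -3.3 points per step over 24 months. The upper end exceeds the 3-point step that 6.3 says the trial can detect. The direction follows from the schedule and the stated model. The size rests on the assumed linear trend, the sustain phase coded as dose 3, the reading of month as crossed or nested, the assumed truncated schedule for the first-year data, and a linear approximation on site-month proportions. The power claim in 6.3 is correct for the model it used, but it does not carry over to a model that isolates the randomised comparison.

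**What to change.** In 6.1, make calendar month (or six-month period) a fixed categorical effect in the primary model, keep the site and practice-group intercepts random, and state that this model applies to the November 2018 to March 2020 data. Cohort contrasts within the same period would serve the same purpose.

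Restate 6.3 under that model. The claim of more than 80% power at 3 points per step must be withdrawn or recomputed: on the 24-month design it becomes about 11-15%, with an 80%-power step of about 10-12 points. The assumed first-year schedule is less precise still (2.80 x 5.5 = about 15 points per step).

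This cost is substantive and uneven across the aims. The hypothesised 50% reduction from 73% is 36.5 points, well above these thresholds. If the further 15% reductions are relative, they are 0.15 x 36.5 = 5.5 points and 0.15 x 31.0 = 4.7 points, which fall below them. The protocol should say so.
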